#### Other Measures That Characterize the Sample

The Columbia-Suicide Severity Rating Scale (C-SSRS) screener [106-113] assesses recent suicidal behavior, including preparatory behavior, and aborted, interrupted, and actual attempts. To maximize readability, the pediatric or cognitively impaired C-SSRS version [114] was selected for this study, and additional items were developed and added to gather additional details on suicidal behavior. The C-SSRS screener has strong psychometric properties demonstrated in general [113] and veteran [108] populations, is used in the Defense Health Agency’s Behavioral Health Data Portal [115]**,** and has shown predictive validity for suicidal behavior. The eligibility criterion for recent SI is having SI in the past month or making an aborted, interrupted, or actual suicide attempt in the last month.

Participants report their usual sleep and wake schedules at baseline, follow-up, and on the last day of each week of EMA. Items from the Consensus Sleep Diary [116] and the Patient-Reported Outcomes Measurement Information System (PROMIS) Sleep Disturbance Scale [117,118] ask about recent sleep quantity and quality. The Consensus Sleep Diary was shown to be a valid and reliable measure of sleep in multiple studies [119-121] while the PROMIS Sleep Disturbance scale was shown to have good face and construct validity, convergent validity, and internal consistency reliability [118].

Various protocols from the NIH-funded PhenX Toolkit’s Social Determinants of Health Core Collection [101] are used to assess demographic characteristics, such as age, gender identity, sexual orientation, race, ethnicity, living situation, occupation, and highest education received. They are supplemented with military-specific questions, such as branch, rank achieved, military occupation, deployments, and services in Reserves or National Guard.

### Data Analysis

#### Power and Sample Size

We plan to recruit 510 participants with the aim of holding type I (α=.05) and type II error rates (β=.05; power=0.95) at equal levels. For aim 1.1 with 3 conditions and 2 assessment time points, a sensitivity power analysis conducted using the *pwr* package in the R software (R Foundation for Statistical Computing) indicated that our proposed sample size will provide sufficient power to detect moderate effect sizes, with the smallest detectable effect size being f^2^=0.17. For aim 1.2, our proposed sample size will provide sufficient power to detect small effect sizes, with the smallest detectable effect size being f^2^=0.03. On the basis of the prevalence rate for SI in US military service members and veterans between 13.9% and 14.1% and between 1.9% and 2.4% for suicide attempts [122], we expect that 13.9% (71/510) of our proposed full sample will report current SI.

For aim 3, comparing the 2 primary conditions (n=340), with a 7-day assessment period and 3 assessments per day (total observations, n=21), power analysis using the *EMAtools* R package shows sufficient power (0.95) to detect moderate (Cohen *d=*0.5) to large (Cohen *d*=0.8) effects within a month at α=.05, even with a 50% response completion rate. For the full year of the monthly 7-day assessment period (total observations, n=252), the same analysis similarly indicates sufficient power to detect moderate to large effects across 12 months. For aim 4, the recommended sample size is for a 2-level mediation model based on Monte Carlo simulations [123] or detecting small effects with adequate power (0.8) while holding the type I error rate at α=.05, when there are at least 3 assessments per participant, are between 215 and 257 participants if within-participant correlations are moderate (intraclass correlation coefficient [ICC]=0.1),300 to 438 participants if within-participant correlations are moderate (ICC=0.4-0.6), and 495 to 544 participant if within-participant correlations are high (ICC=0.9). Notably, as within-participant observations increase, the required sample size to achieve adequate power decreases. With 12 within-participant observations, our required sample size would be smaller than the recommended sample size [123]. Altogether, 510 participants and 252 assessments per participant over the course of the study should provide sufficient power to detect the hypothesized between- and within-participant effects.

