### Randomization

A randomization module with participants stratified into 2 levels (recent suicidality vs no recent suicidality) and randomized into 3 conditions (Caring Contacts with EMA, Caring Contacts alone, and EMA alone) was built into REDCap. Recent suicidality is indicated by a participant endorsing that they have either wished they were dead or had thoughts of killing themself sometime in the past year. This module is programmed to randomize participants with no involvement of study staff to prevent potential bias, with intervention and control assignments distributed evenly across participants. Once participants have completed the online baseline survey, they are randomized into 1 of the 3 conditions (Table 1; Figures 1 and 2). Further details on the EMA procedures are provided in subsequent sections.

**Table 1 table1:** Assessment and intervention message timeline^a^.

Study procedure		Study condition		
		CC^b^ and monthly EMA	CC only	Monthly EMA only
Consent and baseline survey		✓	✓	✓
Two weeks of baseline EMA^c^		✓	✓	✓

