#### Analysis Plan

First, descriptive statistics will be calculated for all variables and group differences in baseline variables will be examined to ensure randomization success. All outcome variables will be examined for nonnormality, and given past suicide research, we anticipate a positive skew for suicidal thoughts and behaviors, and we will use an appropriate model for all analyses based on the distribution of the outcome variables. On the basis of a Directed Acyclic Graph model generated using DAGitty [124,125], demographic variables are conditionally independent of our outcome variables after accounting for the variables specified in our aims and thus do not confound the relationship between the Caring Contacts intervention and our outcome variables. However, to understand the nuanced effects of Caring Contacts on suicide risk across diverse subgroups, we will control for ethnicity, gender, and military status (veteran vs current US military service member) as covariates in our analysis. This stratification allows us to discern potentially differential impacts of the intervention and ensures that our findings are robust and applicable across the varying demographic profiles within the veteran population. Furthermore, all analyses will be conducted using an intent-to-treat framework, using all available data, and using robust maximum likelihood estimation to account for missing data.

For aim 1.1, individual participant means and SDs of each suicide indicator (motivation to live, passive ideation, active ideation, suicide intent, and urges to harm self) will be calculated from the baseline and 12-month EMA period (for all conditions). Then, to assess group differences in the outcome measures of interest, an analysis of covariance examining condition-specific differences at 12 months, controlling for baseline values of the outcome variable of interest, will be conducted. Preplanned post hoc comparisons will compare (1) any Caring Contacts (combined) to no Caring Contacts, (2) Caring Contacts with and without EMA, and (3) EMA with and without Caring Contacts.

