For those participants who will complete EMA for all 12 months (n=340), we will conduct an *exploratory analysis* of changes over time in the mean and intraindividual SD of suicide outcomes. The unique and intensive sampling approach of EMA allows for fine-grained exploration of if and when outcomes change in a clinical trial. Specifically, we will first visually examine trajectories by condition to determine the shape of change *trajectories* over time. Then, following the determination of the shape, we will conduct a linear mixed effects growth model (eg, linear, nonlinear quadratic, and piecewise) [126-129], including a dummy-coded condition variable (with EMA only as the reference) as a predictor of both intercept and slope to determine how intervention condition impacts change in suicide outcomes over time.

For aims 1.2 and 3, to examine secondary suicide outcomes and measures of psychological distress, we will use analysis of covariance to examine condition-specific differences in continuous scores of suicide ideation and cognitions and examine group differences at 12 months, controlling for baseline values of the outcome variable of interest. Similarly, preplanned post hoc comparisons will compare (1) any Caring Contacts (combined) to no Caring Contacts, (2) Caring Contacts with and without EMA, and (3) EMA with and without Caring Contacts. For both aims 1.1 and 1.2, any baseline variables that were not successfully randomized will be included as covariates in the regression models.

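### The smallest detectable effect for aim 1.1, printed as f²=0.17, appears to be Cohen's f; on the f² scale it is 0.03, the same as for aim 1.2

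*Protocol article*

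**What the plan says.** All of the power inputs are in the protocol article, section Power and Sample Size. The sample is given as "We plan to recruit 510 participants", with error rates set by "holding type I (α=.05) and type II error rates (β=.05; power=0.95) at equal levels". The primary EMA calculation is introduced by "For aim 1.1 with 3 conditions and 2 assessment time points", and its result is "sufficient power to detect moderate effect sizes, with the smallest detectable effect size being f^2^=0.17". The next sentence gives the result for aim 1.2: "sufficient power to detect small effect sizes, with the smallest detectable effect size being f^2^=0.03".

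The Randomization section describes the allocation as "with intervention and control assignments distributed evenly across participants", that is, 170 per arm. In the Analysis Plan, aim 1.1 is to be tested by "an analysis of covariance examining condition-specific differences at 12 months, controlling for baseline values of the outcome variable of interest". For aims 1.2 and 3 the same section says "we will use analysis of covariance to examine condition-specific differences in continuous scores of suicide ideation and cognitions", again at 12 months and adjusted for baseline. The same three follow-on contrasts are listed for both aims.

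**The concern.** The two aims share the model, the number of arms, the sample size, alpha and power. A sensitivity analysis with identical inputs has one answer, yet the article prints two that differ more than fivefold and attaches different verbal labels to them (moderate and small). The larger figure belongs to the primary EMA outcomes.

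What is at stake is how the design is read. Taken at face value, f²=0.17 is f=√0.17=0.41. A reader would conclude that the primary analysis can reliably find only effects of that size, and that the survey outcomes are far better powered than the EMA outcomes. Anyone reusing the figure to plan another trial would carry the error forward.

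**Working it through.** **Inputs.** N=510, alpha 0.05 and power 0.95 (Power and Sample Size); three equal arms of 170 (Randomization); a condition effect with 2 degrees of freedom (Analysis Plan).

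**Method.** Under the alternative, the F statistic is noncentral F with 2 and 507 degrees of freedom and noncentrality λ = N·f². Solve for the f at which the probability of exceeding the 5% critical value is 0.95.

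**Attempt to reproduce the stated figures.**
- Critical value F(2, 507) = 3.01.
- 95% power needs λ = 15.53.
- f² = 15.53/510 = 0.0305, so f = √0.0305 = 0.1745.
- The regression form with 2 numerator and 507 denominator degrees of freedom gives the same f²=0.0305. Removing 1, 4 or 6 further degrees of freedom for covariates leaves f at 0.1745.

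The aim 1.2 figure (f²=0.03) is reproduced. The aim 1.1 figure is not reproduced as f², but 0.17 is what f rounds to. On the f² scale the printed value is 0.17/0.0305 = 5.6 times the computed one.

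**What f²=0.17 would imply.** With λ = 0.17·N, 95% power is reached at N=94 (power 0.950), or at N=96 with equal arms (power 0.954). At N=510 the power exceeds 0.9999. It is therefore not the smallest effect detectable with 510 participants at 95% power.

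**Could another model give f²=0.17?**

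| Variant | Smallest detectable f² |
|---|---|
| 1 to 11 numerator df, N=510 | 0.026 to 0.050 |
| Six cells (3 conditions × 2 times), N=510 | 0.039 |
| Repeated measures, between or interaction effect, correlation 0 to 0.7 | 0.005 to 0.026 |
| 2 df, N=340 | 0.046 |
| 2 df, N=170 | 0.092 |
| 2 df, N=71 | 0.227 |
| 1 df, N=71 | 0.188 |

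None gives 0.17.

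**Effect of attrition on the corrected figure.** The article gives no retention rate for 12-month data, so the range below is an assumption. It is unadjusted for baseline.

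| Retention | N analysed | f | f² | Power at f=0.1745 |
|---|---|---|---|---|
| 100% | 510 | 0.175 | 0.030 | 0.95 |
| 90% | 459 | 0.184 | 0.034 | 0.93 |
| 80% | 408 | 0.195 | 0.038 | 0.89 |
| 70% | 357 | 0.209 | 0.044 | 0.85 |

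**Planned contrasts.** Normal approximation, unadjusted, no loss, two-sided 5%, 95% power: d = (1.960+1.645)·√(1/n₁+1/n₂).
- Any Caring Contacts versus none, 340 versus 170: 3.605·√(1/340+1/170) = 0.34.
- Single arms, 170 versus 170: 3.605·√(2/170) = 0.39.

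**The case against.** The strongest reply is that nothing in the trial depends on this number. The article calls the calculation a sensitivity analysis at a proposed sample size, so 510 is not shown to derive from f²=0.17. The error is conservative, and a nearly correct value for the same sample and model stands in the next sentence. All of this holds, and it limits the point to a correction of reporting. It does not make the printed figure right.

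The cause is also inferred. The article names the R package but not the call. That one quantity rounds to 0.17 as f and to 0.03 as f² makes the mislabelling by far the likeliest explanation. If the cause is something else, f²=0.17 still does not follow from the stated inputs.

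A reader might go further in three ways that the document does not support:
- **That the primary analysis is underpowered, or loses its power as soon as anyone drops out.** The mislabel works in the opposite direction. On the corrected scale power falls gradually, from 0.95 to 0.85 at an assumed 30% loss. Even there f²=0.044 is far more favourable than the printed 0.17.
- **That the lack of an attrition allowance is an error in itself.** A condensed article may leave this to the full protocol. The plan describes retention measures and an analysis of all available data by robust maximum likelihood, although that does not restore lost information. Baseline adjustment would offset some of the loss. With an assumed baseline-to-12-month correlation of 0.55, residual variance falls by a factor 1−0.55²=0.70, which roughly cancels 30% attrition. The article gives no correlation to use.
- **That the power statement addresses the wrong test.** The plan runs the three-condition ANCOVA first and calls the contrasts post hoc, so powering the overall test matches the stated analysis. The detectable d for the contrasts is useful but optional. If only the 170 versus 170 comparison were quoted, it would omit the first-listed contrast, which is the more sensitive one.

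Nor does the error leave a null result uninterpretable: the Analysis Plan commits to 95% confidence intervals for its regressions.

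**Conclusion.** The stated smallest detectable effect for the primary EMA outcomes is wrong as printed and inconsistent with the figure for aim 1.2. With 510 analysed in three equal arms at alpha 0.05 and power 0.95, it is f=0.1745, f²=0.0305. The printed f² is about 5.6 times too large, and the contrast drawn between a moderate effect for one aim and a small effect for the other has no basis. The arithmetic uses only inputs stated in the article; that 0.17 is f printed as f² is an inference.

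The consequence is that the primary analysis looks less sensitive than it is. Sample size, analysis and conduct are unaffected. The attrition figures are secondary and rest on assumed retention of 70% to 90%.

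**What to change.** 1. Check the saved power output for aim 1.1. If it confirms the reading above, replace f²=0.17 with f=0.17 (f²=0.03) and describe it as small to moderate.
2. Use the same figure and the same verbal label for aims 1.1 and 1.2, or explain which input differs.
3. Say that the figure assumes 12-month data from all 510, and restate it at a declared expected retention.
4. Optionally, add the detectable d for the planned contrasts (about 0.34 for 340 versus 170 and 0.39 for 170 versus 170, unadjusted and without loss).

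Keep N=510. The cost is wording, plus a retention assumption that the investigators must supply. The stated sensitivity for aim 1.1 improves on the printed value; once attrition is allowed for, it becomes somewhat less favourable than the f²=0.03 now given for aim 1.2.

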#### Analysis Plan

First, descriptive statistics will be calculated for all variables and group differences in baseline variables will be examined to ensure randomization success. All outcome variables will be examined for nonnormality, and given past suicide research, we anticipate a positive skew for suicidal thoughts and behaviors, and we will use an appropriate model for all analyses based on the distribution of the outcome variables. On the basis of a Directed Acyclic Graph model generated using DAGitty [124,125], demographic variables are conditionally independent of our outcome variables after accounting for the variables specified in our aims and thus do not confound the relationship between the Caring Contacts intervention and our outcome variables. However, to understand the nuanced effects of Caring Contacts on suicide risk across diverse subgroups, we will control for ethnicity, gender, and military status (veteran vs current US military service member) as covariates in our analysis. This stratification allows us to discern potentially differential impacts of the intervention and ensures that our findings are robust and applicable across the varying demographic profiles within the veteran population. Furthermore, all analyses will be conducted using an intent-to-treat framework, using all available data, and using robust maximum likelihood estimation to account for missing data.

For aim 1.1, individual participant means and SDs of each suicide indicator (motivation to live, passive ideation, active ideation, suicide intent, and urges to harm self) will be calculated from the baseline and 12-month EMA period (for all conditions). Then, to assess group differences in the outcome measures of interest, an analysis of covariance examining condition-specific differences at 12 months, controlling for baseline values of the outcome variable of interest, will be conducted. Preplanned post hoc comparisons will compare (1) any Caring Contacts (combined) to no Caring Contacts, (2) Caring Contacts with and without EMA, and (3) EMA with and without Caring Contacts.

For those participants who will complete EMA for all 12 months (n=340), we will conduct an *exploratory analysis* of changes over time in the mean and intraindividual SD of suicide outcomes. The unique and intensive sampling approach of EMA allows for fine-grained exploration of if and when outcomes change in a clinical trial. Specifically, we will first visually examine trajectories by condition to determine the shape of change *trajectories* over time. Then, following the determination of the shape, we will conduct a linear mixed effects growth model (eg, linear, nonlinear quadratic, and piecewise) [126-129], including a dummy-coded condition variable (with EMA only as the reference) as a predictor of both intercept and slope to determine how intervention condition impacts change in suicide outcomes over time.

For aims 1.2 and 3, to examine secondary suicide outcomes and measures of psychological distress, we will use analysis of covariance to examine condition-specific differences in continuous scores of suicide ideation and cognitions and examine group differences at 12 months, controlling for baseline values of the outcome variable of interest. Similarly, preplanned post hoc comparisons will compare (1) any Caring Contacts (combined) to no Caring Contacts, (2) Caring Contacts with and without EMA, and (3) EMA with and without Caring Contacts. For both aims 1.1 and 1.2, any baseline variables that were not successfully randomized will be included as covariates in the regression models.

For aim 2, thematic analysis will be used to systematically examine the qualitative data obtained from the interviews [57,58]. This process will begin with verbatim transcription of the interview audio recordings, ensuring a precise and comprehensive dataset. An inductive approach will be adopted, allowing themes to emerge organically from the data without preconceived categories. The research team will use open coding, assigning descriptive codes to individual text segments within each transcript. This initial coding will facilitate the identification of patterns and key themes related to participants’ experiences and perceptions of the Caring Contacts intervention. To ensure accuracy and consistency, intercoder reliability will be established through regular team meetings where coding decisions are discussed and consensus is reached. This iterative process will continue as new codes emerge, with the team members actively refining and redefining codes to capture the nuances of the data accurately. Following open coding, the research team will engage in axial coding, grouping codes into broader categories to elucidate connections and relationships between them. This step lays the foundation for developing overarching themes that encapsulate the study’s core insights. Finally, the coded data will be systematically reviewed and organized to refine these themes and develop a coherent narrative that accurately reflects the participants’ experiences. Triangulation methods will be used throughout this process, comparing information from different participant groups and cross-referencing existing literature to validate the findings and ensure their robustness and reliability.

For aim 4, to examine potential mechanisms of Caring Contacts, we will use the within-EMA period data and examine within-participants mediation using dynamic structural equation modeling (with random intercepts and slopes) [130]. Dynamic structural equation modeling allows for the simultaneous estimation of within- and between-person effects that allow for idiographic mechanistic models over time, which can be ideal for answering questions about within-participant mechanisms of suicide outcomes. In line with recommendations for intensive longitudinal data analysis, all hypothesized mechanism variables (ie, mattering, personal and social responsibility, perceived burdensomeness, and entrapment) will be centered at both the between-person and within-person mean level. Then, within-person regression models will be run to examine the relationship between the hypothesized mechanisms and suicide outcome, using a lag-1 model and autoregressive covariance structure to account for assessments closer in time to be more highly correlated. Next, to examine the mediation effect of treatment condition on outcomes through the hypothesized mechanisms, we will estimate within-level indirect mediation effects, calculated as the product of the within-level effect of treatment condition on the mechanism (a path) and the effect of the mechanism on the suicide outcome. All mediation analyses will be examined at the within-person level (1-1-1), excluding cross-level mediation. Random starts will be used for all models to replicate the best log-likelihood. Finally, to examine the immediate versus delayed impact of the timing of Caring Contacts intervention, we will use autoregressive modeling to examine the direct impact on stress, distress, and suicide outcomes immediately following a Caring Contacts message compared to times without a message, using the EMA data. For all regressions, 95% CIs will be reported, and statistical significance will be set at *P*<.05.

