## Methods

### Study Design

In this randomized controlled trial (RCT), we will examine the impact of the Caring Contacts intervention delivered through SMS text message across a large, diverse sample of veterans and service members who are stressed (external factors) or distressed (internal factors). This trial is conducted entirely online and will recruit veterans and service members (N=510). To ensure that all participants experiencing stress or distress have access to needed resources (enhanced usual care), each participant, regardless of condition, is provided a tailored set of resources to match their needs (eg, housing, finances, employment, food insecurity, and socialization). Participants are stratified based on whether they endorsed SI in the past year and randomly assigned to 1 of 3 study conditions, including receiving either Caring Contacts, EMA, or both, for the 12-month study period. Given that the frequency of messages and the self-monitoring process inherent to EMA may have its own effect on our outcome variables, we included a Caring Contacts–only condition to isolate the effects of Caring Contacts and EMA. The study design and methods were evaluated during an acceptability and feasibility pilot study, during which we also developed a web-based app platform custom-made for Caring Contacts (manuscript in preparation). The study staff worked with employees housed within a local veteran service organization and an outpatient psychiatry clinic to develop study procedures and the Caring Contacts intervention. From this feedback and use data, adjustments to the protocol, intervention, and EMA procedures were made before the launch of this RCT.

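### The stated outcome models leave out the stratification factor, past-year suicidality, and for aims 1.1 and 1.2 add covariates by an undefined imbalance rule

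*Protocol article*

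**What the plan says.** **Stratification.** The Randomization section describes the allocation as "A randomization module with participants stratified into 2 levels (recent suicidality vs no recent suicidality) and randomized into 3 conditions". The recent-suicidality level covers anyone who has "either wished they were dead or had thoughts of killing themself sometime in the past year". Study Design agrees: "Participants are stratified based on whether they endorsed SI in the past year". Allocation is even across the three conditions, about 170 each of 510.

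**Outcome models.** For aim 1.1 the Analysis Plan specifies an ANCOVA at 12 months, "controlling for baseline values of the outcome variable of interest, will be conducted". Aims 1.2 and 3 use the same form. Across the analyses, "we will control for ethnicity, gender, and military status (veteran vs current US military service member) as covariates in our analysis". The stratum is named in none of these models, nor in the exploratory growth model.

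**Imbalance rule.** The Analysis Plan begins by comparing baseline variables between groups as a check on the randomisation. It later adds, for aims 1.1 and 1.2, that "any baseline variables that were not successfully randomized will be included as covariates in the regression models". It gives no criterion for a failed variable and no list of candidates.

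**The concern.** There are two separate weaknesses.

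1. A factor used to restrict the randomisation belongs in the analysis model. Stratification removes chance differences between arms on that factor. A model without it still counts the variance between strata as noise, so the reported SE is larger than the true sampling variability. At stake are a little precision and a test that runs below its nominal level.

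2. Allocation is done by an automated REDCap module without staff involvement, so baseline differences between arms are chance, and examining them cannot show whether randomisation worked. Choosing covariates by imbalance ignores how strongly they predict the outcome. Because the criterion is undefined and analysis follows data collection, the added covariates can be settled when allocation and outcomes are both known.

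The two combine badly: stratification balances the stratum by design, so the imbalance rule is unlikely ever to bring it in.

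**Working it through.** **The plan's own figure.** Inputs from Power and Sample Size: N = 510, three conditions, α = 0.05, power 0.95. For a noncentral F with 2 and 507 degrees of freedom and λ = N × f², the smallest detectable effect is f² = 0.0305. This reproduces the f² = 0.03 stated for aim 1.2 (power at exactly 0.03 is 94.7%). The 0.17 stated for aim 1.1 does not reproduce as f²; that is a separate matter and is not used here. The article gives no figure for the stratum's contribution, so a range is needed.

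**Cost of omitting the stratum.** Let R² be the share of residual variance that the stratum explains after the baseline outcome and the other covariates. This is assumed.

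- SE with the stratum relative to SE without: √(1 − R²).
- Under stratified allocation the test statistic without the stratum has variance 1 − R² instead of 1, so its true size is 2 × [1 − Φ(1.96/√(1 − R²))].
- Power is shown for any Caring Contacts (340) against none (170) at an illustrative d = 0.30. The SE is √(1/340 + 1/170) = 0.0939, so δ = 0.30/0.0939 = 3.194. Power is Φ((δ − 1.96)/√(1 − R²)) without the stratum and Φ(δ/√(1 − R²) − 1.96) with it.

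| Assumed R² | SE ratio | SE smaller by | True size of a 5% test | Power without → with stratum |
|---|---|---|---|---|
| 1% | 0.9950 | 0.5% | 4.9% | 89.3% → 89.4% |
| 2% | 0.9899 | 1.0% | 4.8% | 89.4% → 89.7% |
| 5% | 0.9747 | 2.5% | 4.4% | 89.7% → 90.6% |
| 10% | 0.9487 | 5.1% | 3.9% | 90.3% → 92.0% |

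Worked example at 5%: √0.95 = 0.9747; 1.96/0.9747 = 2.011; 2 × [1 − Φ(2.011)] = 0.0443.

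**The imbalance rule.** Stratified 1:1:1 randomisation was simulated (N = 510, 2,000 to 4,000 runs per setting) with 20 mildly prognostic baseline variables. The variable count, their strength and the thresholds are assumptions.

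- Under the null, adding every variable imbalanced at a fixed 0.05 gave type I error of 4.2% to 4.8%, so no inflation.
- Under the null, taking the most favourable of five options (no added covariates, or thresholds of 0.01, 0.05, 0.10 or 0.20) gave 6.4% to 7.4%.
- Under the null, the model with neither stratum nor added covariates ran at 4.8% to 5.4%. With a simulation error of about √(0.05 × 0.95/4000) = 0.3 percentage points, that cannot be told from 5%. The stratum's direct effect was set small or zero in these runs.
- At a true effect of 0.2 in the simulation's units, power was 75.7% with baseline adjustment only, 77.1% with the stratum added, 76% under the imbalance rule, and 85% with the stratum and all 20 covariates prespecified. Most of that last gain comes from the prognostic covariates, not the stratum.

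**The case against.** **Small loss.** The ANCOVAs already adjust for the baseline outcome. For aim 1.1 that is an average of up to 42 momentary reports, which should carry much of what the stratum knows. Only the remaining contribution counts. With an even stratum split, R² of 5% or 10% needs a gap between strata of about √(0.05/0.25) = 0.45 or √(0.10/0.25) = 0.63 residual SD after adjustment. This stands: the lower rows of R² (1% to 5%) are the likelier ones. A reader might take R² = 20% and infer SEs inflated by 12% and a test at 2.8%, but that needs a gap of 0.89 SD, and nothing in the article supports it.

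**Bias or false positives.** A reader might infer that omitting the stratum biases the result or inflates type I error. It does neither; the error is on the conservative side.

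**A primary model chosen after seeing data.** A reader might infer this from the imbalance rule. The ANCOVA form, baseline adjustment, three demographic covariates and three contrasts are all stated in advance. The rule leaves only the added covariates open, and only for aims 1.1 and 1.2. The 6.4% to 7.4% error rate needs deliberate selection of the best result, which the article does not propose.

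**How often the rule fires.** With 20 or 30 independent variables tested at 5%, at least one would be flagged with probability 1 − 0.95^20 = 64% or 1 − 0.95^30 = 79%. The article states no test, no threshold and no count, and its distress scales overlap, so independence is implausible. The figure would also count added covariates, not harm.

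**A condensed article.** The demographic sentence is not the whole covariate list, and an unseen SAP may name the stratum and define the rule. This stands in part. But the article commits itself to a list and a selection rule, and both can be judged as written.

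**Conclusion.** The point holds in limited form. The stratification factor is absent from every stated outcome model, and the rule for adding covariates in aims 1.1 and 1.2 selects on chance imbalance with no defined criterion.

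The statistical cost of the first part is small: an SE reducible by 0.5% to 5.1% and a nominal 5% test running at 4.9% down to 3.9%, for an assumed partial R² of 1% to 10%. If the baseline score captures nearly all of the stratum's information, the cost is close to zero. The estimate is unbiased either way.

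The second part is a matter of discretion, not demonstrated error inflation. A fixed threshold kept type I error at or below 5% in the simulated settings; the weakness is that none is fixed. The change is worth making because it costs almost nothing, not because the primary result is in danger.

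**What to change.** - Add the past-year suicidality stratum to the ANCOVAs for aims 1.1, 1.2 and 3. Add it as a covariate to the exploratory growth model too, without also adding the baseline outcome there if baseline is one of the modelled time points.
- Fix the ANCOVA covariate list as baseline outcome, stratum, ethnicity, gender and military status, plus any further prognostic covariates named in advance.
- Delete the imbalance rule, or keep it as a sensitivity analysis with a stated criterion and candidate list.
- Present baseline data by arm descriptively, not as a check on randomisation.

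The stratum is already recorded in REDCap, so the cost is one degree of freedom among 510 participants and a change of wording. Lock it before outcomes are compared by arm.
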